## Abstract

**Abstract:**

**Introduction:**

During pregnancy, physiological and psychological factors influence eating behaviour and food preferences. Food cravings are common in pregnancy and contribute to excessive gestational weight gain (GWG). Excessive GWG is present across all body mass index (BMI) categories and is associated with adverse outcomes. Outside of pregnancy, highly palatable food cues activate brain regions involved in reward and attention, which may influence eating behaviour and behavioural responses. However, brain and behavioural responses to food cues across pregnancy, and their association with psychological and metabolic factors, remain poorly understood. This study aims to investigate spatiotemporal brain responses to visual food cues across individuals with different BMI categories and their associations with behavioural, psychological and metabolic outcomes during pregnancy.

**Methods and analysis:**

This is a prospective observational cohort study conducted at the Lausanne University Hospital, Switzerland. 94 pregnant individuals (47 healthy normal weight and 47 with overweight/obesity) will be assessed at 12–16 and 31–36 weeks of gestational age from November 2024 to September 2026. Data collected for the primary outcomes include electroencephalography-based brain responses to validated visual food cues varying in fat and carbohydrate content, behavioural responses to the same cues using a gamified smartphone Go/NoGo task. Secondary validated outcomes include heart rate variability (Actiheart), body composition (InBody S10), glycated haemoglobin (Afinion), cardiorespiratory fitness (The Chester step test), snack intake, eating behaviour (Intuitive Eating Scale-2, Three-Factor Eating Questionnaire-Revised), food cravings (Food Craving Questionnaire-state), mood and depressive symptoms (Edinburgh Postnatal Depression Scale). Statistical analyses include group comparisons, longitudinal analyses and regression models adjusted for potential sociodemographic/medical confounders.

**Ethics and dissemination:**

All participants will provide written informed consent. The Human Research Ethics Committee of the Canton de Vaud approved the study protocol (CER-VD 2023-01462). Findings will be disseminated through peer-reviewed publications, (inter)national conferences and shared with healthcare professionals and stakeholders to inform strategies for improving maternal health.

Strengths and limitations of this studyThis study uses a multimodal approach to investigate pregnancy-related food cravings by combining self-reported with neurophysiological, behavioural psychological and physiological measures.Longitudinal design enables assessment of food cravings and brain responses to visual food cues across pregnancy.The relatively small sample size is consistent with comparable electroencephalography studies but may limit statistical power for subgroup or multivariable analyses.Due to limited availability of neurophysiological and behavioural data on food cue responses in pregnancy, several analyses are exploratory.The recruitment strategy and the requirement for multiple assessments may have introduced selection bias, potentially limiting the generalisability of the findings.

## Introduction

 Pregnancy is a period marked by many physiological and hormonal changes that are likely to influence eating habits, with an increase in appetite, food cravings and energy intake.^1^ Food cravings increase in frequency and intensity during pregnancy,^2^ with approximately 80% of pregnant women reporting food cravings at the end of the first trimester.^3^ They refer to strong urges for specific foods and are recognised as important contributors to overweight and obesity (OW/OB), excessive gestational weight gain (GWG) and failure to sustain weight loss in the postpartum period.^4^ The prevalence of excessive GWG for women of all prepregnancy body mass index (BMI) categories is between 37% and 64%.^5^ Excessive GWG is associated with long-term weight retention^6^ and increases the long-term risk of cardiometabolic morbidity and mortality.^7^ This is even more important in view of the globally rising prevalence of obesity that affects 35.7% of women within the reproductive age in the USA.^8^

Psychological states such as stress, mood and emotions may further influence eating behaviours, including the quality of food intake. Both stress and emotions have an impact on eating behaviour during pregnancy, including the increased risk of consuming food with higher energy density and less nutritional value.^9^ Similarly, negative mood states and higher levels of depressive symptoms and stress are associated with more frequent and intense self-reported reward-related eating and addictive-like eating and food cravings.^10–12^

Food cravings might further be influenced by regular physical activity. In the general population, an association between regular moderate-to-vigorous physical activity and reduced wanting for high-fat food was found.^13^ In pregnancy, physical activity showed benefits for preventing adverse pregnancy outcomes, such as excessive GWG or gestational diabetes mellitus (GDM).^14^ A cohort of women followed from their first to third trimester of pregnancy with normal weight (NW) or with obesity found high physical activity levels to be associated with higher levels of circulating soluble leptin receptor in both the second and third trimester, suggesting a potential association between exercise, reward-related pathways and neuroendocrine regulation of food intake.^15–17^

Neurobiological research in rodents demonstrates that pregnancy induces a reorganisation of key components of the dopaminergic mesolimbic circuitry promoting craving-like behaviour and an increased intake of palatable foods.^18^ However, to our knowledge, there is no clear understanding of the brain mechanisms underlying food cravings during pregnancy in humans. Highly palatable foods, such as those high in sugar or fat, are known to trigger the reward system and promote overeating.^19^ A study found that self-reported cravings for high-fat foods triggered by emotional cues are particularly linked to excessive GWG.^20^ Such palatable foods activate limbic and striatal reward pathways, increasing the tendency to seek and consume them.^21^ Speed of motor responses in discrimination tasks, such as Go/NoGo, may reflect the reward system’s sensitivity to food cues. The more motivational value a cue has, the faster the motor response.^22^ However, there is a lack of knowledge regarding behavioural and brain responses to food cues during pregnancy in humans.

Research outside of pregnancy has shown that the human brain can discriminate the energy value of foods when viewing food images, particularly fat content. Cues of ‘high’ versus ‘low’ fat foods elicit differential brain responses in both strength and topography, especially in prefrontal cortical regions involved in reward evaluation and decision-making.^23^ Other neuroimaging studies have shown that the dorsolateral prefrontal cortex plays a key role in cognitive control of hunger, appetite, and reward evaluation, and reduced activation in the region has been associated with obesity and poorer appetite regulation.^24
25^ Furthermore, the brain’s response to food stimuli differs between women with different weight categories: women with overweight showed increased visual evoked potentials (VEPs) in the right frontal and central cortices, which are markers of an increased sensory alertness and a heightened visual cue-reactivity, not allowing to downregulate later responsivity.^26^

The above-mentioned research on food cravings during pregnancy has been based on questionnaires assessing different types of food cravings and their occurrences.^10–12
19
20^ However, no study has yet identified any underlying mechanisms to objectively describe or explain the cause of cravings during pregnancy.

## Aims

The overall aim of this study is to investigate brain responses to food viewing in the beginning of the second and the third trimesters of pregnancy and their relationship with metabolic health. We will investigate this in pregnant individuals with NW and with OW/OB, which are at higher metabolic risk.

Primary objectives:To investigate differences in brain and behavioural responses to food pictures of varying fat and carbohydrate content: high-fat/high-carbohydrate (HFHC), high-fat/low-carbohydrate (HFLC), low-fat/high-carbohydrate (LFHC) and low-fat/low-carbohydrate (LFLC) during pregnancy, in women with and without OW/OB.To investigate the relationships between brain responses to food pictures as measured by electroencephalography (EEG) and the behavioural responses to food cues measured with a smartphone-based Go/NoGo task in these individuals.Secondary objectives in the same population:To determine the relationships between brain responses to food pictures and different emotional states and stress levels.To investigate differences in brain and behavioural responses to food and non-food pictures.To investigate longitudinal changes in brain and behavioural responses to food pictures of varying fat and carbohydrate content from early to late pregnancy.To investigate the cross-sectional and longitudinal relationships between brain responses to food viewing with eating behaviour, metabolic health and mental health during pregnancy.

## Methods

### Study design

This is a prospective observational study of pregnant individuals with and without OW/OB. Participants will complete two study visits at the Lausanne University Hospital during pregnancy: one during the second trimester (12–16 weeks gestational age (GA)) and the second visit during their third trimester (31–36 weeks GA, see figure 1 for details).

**Figure 1 F1:**
[figure not shown]
Flow chart of the study procedure. *During the snack break participants’ eating behaviour will be recorded with an objective eating behaviour recognition device while participants can choose to consume any of the eight provided snacks. ◊3 days in the morning awakening, 3 days in the evening before going to sleep as well as three times when specifically stressed or in a particularly aroused mood during 10 days after each visit. A-MMS, adapted version of the Multidimensional Mood Scale; EEG, electroencephalography; EHI, Edinburgh Handedness Inventory; EPDS, Edinburgh Postnatal Depression Scale; FCQ-S, Food Cravings Questionnaire-State; HbA1c, glycated haemoglobin; IES-2, Intuitive Eating Scale-2; TFEQ-R18, Three-Factor Eating Questionnaire-Revised 18.

### Study population and eligibility criteria

A total of 94 participants with valid data for the primary outcomes will be included. The study will include two groups of participants based on their prepregnancy BMI, one including individuals with NW and a second group of individuals with OW/OB. Recruitment will be done through flyers in the Lausanne University Hospital and various ambulatory regional hospital clinics as well as private obstetrics and gynaecology practices in the canton of Vaud. Eligibility will be determined during recruitment using a screening questionnaire before enrolment. Participants will self-report all inclusion and exclusion criteria. For both groups, inclusion criteria will include pregnant women with GA between 12 and 16 weeks, aged ≥18 years, and willingness and ability to provide signed informed consent. Additional inclusion criteria for the NW group will be: prepregnancy BMI <25 kg/m^2^, no restrictive diets during pregnancy, no weight changes exceeding 5 kg in the past 5 years (excluding pregnancy), and weight gain within 2 kg during the first trimester, in accordance with the National Academy of Medicine recommendations at the time of inclusion.^27^ Inclusion criteria for individuals in the OW/OB group will be prepregnancy BMI ≥25 kg/m^2^.

Exclusion criteria will include pre-existing diabetes, a diagnosis of an eating disorder (eg, anorexia nervosa, bulimia nervosa or binge-eating disorder), vegetarian or vegan diet (to ensure familiarity and exposure to all food categories), uncontrollable nausea and vomiting during the first trimester of pregnancy, history of bariatric surgery, participation in an intervention study, diagnosed mental illness or use of medication to treat psychiatric disorders, as well as active suicidal thoughts and having an implanted cardioverter-defibrillator.

### Primary outcomes

The primary outcomes of this study include EEG brain responses to food categories of varying fat and carbohydrate content (HFHC, HFLC, LFHC and LFLC), characterised by the VEP latency, amplitude, duration, topography and neural source activity localisation. Additional primary outcomes include the speed and accuracy of the behavioural responses to food categories of varying fat and carbohydrate content (HFLC; HFHC; LFLC; LFHC) measured by a Go/NoGo smartphone task.

### Secondary outcomes

The secondary outcomes include weight, glycated haemoglobin (HbA1c) and body composition. We will also investigate eating behaviour through self-reported questionnaires including food cravings (Food Craving Questionnaire-state, FCQ-s), intuitive eating (French Intuitive Eating Scale-2, IES-2), external, emotional eating and cognitive restriction (Three-Factor Eating Questionnaire-Revised 18, TFEQ-R18). We will measure eating rate using an objective eating behaviour recognition device and subjective questions (self-reported eating rate). We will measure the current mood (Adapted Multidimensional Mood Scale, A-MMS), current level of perceived stress (single-item) and depressive symptoms (Edinburgh Postnatal Depression Scale, EPDS). We will measure heart rate (HR) and heart rate variability (HRV) using an Actiheart. We will finally investigate aerobic fitness using the Chester Step Test (CST).

### Data collection and study visits

The first participant attended the first visit in November 2023 at the Lausanne University Hospital. The last participant is expected to be recruited in May 2026, and all data are expected to be collected by September 2026. The first visit will take place between 12 and 16 weeks of GA, and the second visit will take place between 31 and 36 weeks of GA.

After signing the informed consent, a first phone call will be scheduled, where participants will be asked to provide information about their medical history and lifestyle behaviour. At the end of the phone call, participants will fill out an online questionnaire, including several validated questionnaires (figure 1).

Before each visit, participants will be asked to eat a balanced meal around 12:00 (based on the Swiss Society for Nutrition recommendations, containing a source of carbs, proteins and fibres and avoid fast food or sugary beverages) to minimise the bias of different satiety levels and will be invited to come to the Lausanne University Hospital at 13:30. The testing will be completed at 16:00 and will include several breaks (figure 1).

### Patient and public involvement

Individuals participating in our previous study^28^ expressed a high level of interest in the use of EEG as an objective measure for neurobehavioural responses during pregnancy. A subset of participants (n=16) was asked in semistructured interviews to cite the most meaningful aspects to research in the perinatal period. Based on thematic analyses, the most important research areas for the 16 women were GWG (n=14), nutrition in the perinatal period (n=14), eating behaviour (n=8) and cravings (n=5). Further interests reported by participants included postpartum weight retention and emotional changes during pregnancy. This feedback shaped our present study and primary research questions to gain knowledge on objective measures for food cravings and eating behaviour during pregnancy and their impact on mental and metabolic health.

### Measures

Except for sociodemographic data, all measures will be collected at both visits (see figure 1 for details).

#### Food categories

Across the entire study, both the food pictures and food items are classified into four categories based on their fat and carbohydrate content. The categories are HFHC, HFLC, LFHC and LFLC. Foods were classified as high-fat (>5 g of fat per 100 g (21.6±13.77 g/100 g)) or low-fat (<5 g of fat per 100 g (1.1±1.29 g/100 g)) and as high-carbohydrate (>15 g of carbohydrates per 100 g (48.57±21.13 g/100 g)) or low-carbohydrate (<15 g of carbohydrates per 100 g (4.59±4.59 g/100 g)).

#### EEG: stimuli and apparatus

Participants will be presented with four blocks of trials containing a total of 240 pictures. Each block will contain 50 food pictures of the four food categories and 10 non-food objects that were selected from a larger food picture database.^29^ All pictures will be standardised in size and controlled for low-level visual properties.^23
30^ Each picture will be presented for 500 ms, with block order randomised across participants. A central fixation cross will be displayed during interstimulus intervals to minimise eye movements. The experimental session will take place in a sound-attenuated booth (WhisperRoom model 102 126E). Visual stimuli will be presented on a 27-inch LCD monitor (HP EliteDisplay E273q, 2560×1440 pixels, 60 Hz). Continuous EEG data will be recorded at 1000 Hz using a 128-channel gel-based electrode cap connected to an EEGO mylab system (ANT Neuro; https://www.ant-neuro.com). The online reference will be an electrode at the vertex. Electrodes in the cap are spaced equidistant to one another.

#### Behavioural task during EEG recording

Participants will complete a speeded two-alternative forced choice discrimination task across the four previously described blocks of trials, lasting approximately 13 min in total. During this task, participants will indicate whether each cue presented represents a food or a non-food item by pressing a button on a response box with their dominant hand (button ‘1’ for food pictures, button ‘2’ for non-food object pictures). The block order will be randomised across participants.

The experimenter will first provide a detailed explanation of the task, followed by a brief practice session with seven food and three non-food pictures to familiarise participants with the procedure. Additionally, short on-screen instructions will be presented at the start of each block. Participants will be encouraged to take brief breaks between blocks to reduce fatigue.

Behavioural measures will include the mean response time (RT) (in milliseconds) for correctly identified food and non-food pictures, as well as for each food category. Accuracy (%) will be calculated as the proportion of correctly responded trials. The same selection of food cues will be shown on both visits.

#### Handedness

The handedness of each participant is calculated using the 4-item Edinburgh Handedness Inventory–Short Form.^31^ This is a validated short form of the original questionnaire^32^ where participants indicate their preferred hand for four activities on a 5-point Likert scale from ‘always right’ to ‘always left’. Responses will be recorded from –2 ‘always left’ to +2 ‘always right’ and summed to compute a total handedness score. Participants will be classified as right-handed if total >0, left-handed if total <0 or ambidextrous if total=0.

#### Go/NoGo gamified task

A specific smartphone will be provided to complete a gamified Go/NoGo task lasting a total of approximately 15 min. Participants will be asked to complete this task 10 times in total; once during each of the visits and nine additional times per visit at home. This task will include 24 randomised food cues of varying fat and carbohydrate content (see section ‘Food categories’) circled in green (Go cues), and 4 randomised object cues circled in red (NoGo cues). In total, there will be 70% of Go cues and 30% of NoGo cues. Participants will complete multiple runs of the task each day until they fulfil a daily objective, receiving intermediate scores after each run, and a final score when the objective is achieved.

Before the first game, participants will be asked in the app to answer a liking questionnaire (Visual Analogue Scale (VAS) from 0=strongly dislike to 100=strongly like), where they will rate food images presented during the Go/NoGo task. Before each task, participants will be asked to answer a questionnaire regarding their current mood (A-MMS), current level of perceived stress (single item) and current level of hunger (single item).

During the task, participants will be instructed to respond as fast as possible to the food cues (Go trials) by sliding the image downward with their finger, while withholding their responses to the non-food cues (NoGo trials). If participants respond to a food cue on time (Hit) or correctly withhold their response to an object cue (correct rejection, CR), positive green feedback will be displayed. If participants fail to respond to a food cue within 1.5 s (Miss) or respond to an object cue (false alarm, FA), negative red feedback will be displayed.

As part of the task’s gamified design, and to maintain engagement and adherence, participants who will correctly respond to food cues but exceed the reaction time threshold (RTT, 725 ms) will receive a negative ‘Late’ feedback, while a ‘Down’ feedback will be displayed if the food cues are not dragged to the bottom of the screen.

The behavioural output of the gamified Go/NoGo task will include the response type (Hit, CR, FA, Miss), the feedback (Correct, Incorrect, Late, Down), and the individual reaction time (RT) in milliseconds to each food cue. The outcomes will then be analysed in the percentage of successful trials, total number of errors (FA or missed food cue), number of late (Hit with a RT above the RTT), the mean RT (ms) to food cues, mean RT to each food category (HFLC; HFHC; LFLC; LFHC), total mean RT for food cues and inhibition error (proportion of FA relative to the total of FA and CR).

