##### Analysis of the gamified Go/NoGo task

Raw data from the gamified Go/NoGo task will be collected through The Diner smartphone application and preprocessed using the Diner Data Processor, a Matlab-based processor. For each participant, all raw data files will be extracted directly from the smartphone.

Raw log files will then be analysed and transformed into an Excel dataset for each participant through the processor.

Behavioural data will be imported from Excel files to R running or RStudio will be used^59^ and packages from tidyverse.^60^ Mean RTs will be calculated from the correct responses (Hit trials) for each food item, food category, participant and training day. The food category mean RTs will be calculated by averaging the RT of all items within each food category for each participant and day. Overall RT to food cues will be computed by averaging across all food categories, participants and day. In addition, accuracy measures, including the percentage of correct responses, number of errors, and inhibition error rates (FA/CR+FA)*100, will be computed per participant and per day. Further analyses will include modelling using repeated measures analyses of each day.

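### Go/NoGo accuracy by food category is named a primary outcome, but the planned analysis computes accuracy only per participant and day, and two error outcomes are raw counts over an unfixed number of runs

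*Protocol article*

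**What the plan says.** Under Primary outcomes, the Protocol article names as primary the "speed and accuracy of the behavioural responses to food categories of varying fat and carbohydrate content", measured with the smartphone Go/NoGo task.

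Under Go/NoGo gamified task, every food cue is a Go cue and every NoGo cue is an object. A Miss is a food cue left unanswered for 1.5 s. A false alarm (FA) is a response to an object, and a correct rejection (CR) is a withheld one. A correct food response slower than 725 ms draws Late feedback, and an incomplete drag draws Down feedback.

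The outcome list in that section gives mean RT by food category. It gives no accuracy measure by category. Its success measure is a percentage and its inhibition error is a proportion of FA plus CR, but two entries are counts: "total number of errors (FA or missed food cue), number of late (Hit with a RT above the RTT". The amount of play is not fixed: "Participants will complete multiple runs of the task each day until they fulfil a daily objective".

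Under Analysis of the gamified Go/NoGo task, RT is averaged over Hits by item, category, participant and day. For accuracy, the text says that "accuracy measures, including the percentage of correct responses, number of errors, and inhibition error rates (FA/CR+FA)*100, will be computed per participant and per day".

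The task itself is described with these figures: "This task will include 24 randomised food cues of varying fat and carbohydrate content", alongside four object cues; "In total, there will be 70% of Go cues and 30% of NoGo cues"; and participants are to "complete this task 10 times in total; once during each of the visits and nine additional times per visit at home".

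**The concern.** A primary outcome should be traceable from its name to a variable and an analysis. Speed by category can be traced. Accuracy by category cannot: the analysis section sets its level, and food category is not part of it. If the measure is defined only after the data are in, several versions are open (Misses only, Late included, Down included), and the choice would be made for a primary outcome with results visible.

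The two counts raise a separate problem. If women differ in how many runs they need, a total of errors or lates reflects how long they played as well as how well they played. A comparison of groups, or of days, on such a total cannot separate the two.

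The inconsistent task figures matter less, but they describe how much data each woman contributes and how strongly the task demands withholding.

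**Working it through.** **1. The article's own Go/NoGo calculation.** Sample size calculation gives mean RTs of 550 and 450 ms, SD 63 ms, alpha 0.05 and 80% power, with at least eight per group. The standardised difference is 100/63 = 1.59. The normal approximation 2(1.96+0.84)²/1.59² gives 6.2, so 7. A two-sided t-test needs 7.33, so 8, with power 83.9%. The figure reproduces. It concerns RT only and is not affected by this point; no calculation is given for accuracy.

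**2. From the named outcome to the computed variables.**

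| Measure | Trials used | Divisible by food category? | Divided in the article? |
|---|---|---|---|
| Mean RT | Hits on foods | Yes | Yes |
| Hit/Miss | Foods | Yes | No |
| Late, Down | Foods | Yes | No |
| Success percentage | Foods and objects | Food part only | No |
| Total errors | Misses plus FA | Miss part only | No |
| Inhibition error | Objects | No | No |

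Nothing limits the success percentage to food trials. Read as pooled, it is P = w·H + (1−w)·C, where H is the hit rate averaged over the food trials, C the correct-rejection rate on objects and w the Go share (0.70 as stated). Differences between the four categories are averaged away inside H, and object performance is added in. P therefore cannot stand in for accuracy by food category.

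**3. What counts as a Hit.** The feedback description ties a Hit to an on-time response with positive feedback and gives slow responses a negative Late. The outcome list then defines a late response as a kind of Hit. Whether Late and Down responses are successes is therefore unsettled. This affects accuracy and also mean RT, which is averaged over Hits.

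**4. Counts and exposure.** With error rate e, t trials per run and r runs, expected errors are e·t·r. Two women with the same e differ by the ratio of their runs alone. The article gives none of these three quantities, so all values below are assumptions:
- e = 3%, t = 28: 3 runs give 0.03×28×3 = 2.5 errors and 5 runs give 0.03×28×5 = 4.2, a ratio of 5/3 = 1.67.
- e = 5%, t = 40: 3 runs give 0.05×40×3 = 6 and 6 runs give 0.05×40×6 = 12, a ratio of 2.

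A proportion of trials has expectation e in every case.

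**5. Task figures.**
- Sessions: 2 visits × (1 + 9) = 20. Ten fits only as a number per visit. A footnote in the Figure 1 legend lists 3 + 3 + 3 = 9 occasions in the ten days after each visit, which agrees with nine home sessions per visit if it refers to this task; the figure is not shown.
- Cue share: 24/28 = 85.7% and 4/28 = 14.3% with equal presentation. A 70:30 share beside 24 Go presentations needs 24×0.3/0.7 = 10.3 NoGo presentations. With four object images, each must appear (0.3/4)/(0.7/24) = 2.57 times as often as each food image, for example 24×7 = 168 against 4×18 = 72.
- Inhibition error: typed without the inner bracket, FA = 1 and CR = 3 would give (1/3+1)×100 = 133%. The definition in the outcome list gives 1/(1+3)×100 = 25%.

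**The case against.** The strongest reply is that an article condenses, that the list of accuracy measures is open-ended, and that a fuller analysis plan may define accuracy by category. That would answer mere silence. It does not fully answer this text, which states the level of computation for RT and for accuracy in the same paragraph and includes food category only for RT.

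Several stronger readings might be inferred, and the article does not support them:
- *That accuracy by category cannot be estimated.* Response type and feedback are recorded, and Misses occur on food cues, so Hit/Miss accuracy by category is computable. The primary outcome does not ask for inhibition error by category.
- *That every error measure depends on exposure.* The success percentage and inhibition error already have denominators. Only total errors and number of late lack one, and neither is the by-category primary outcome.
- *That 24 and 4 cues prove 70:30 wrong.* The first pair may count distinct images and the second presentations. The repetition is not stated, so this is an unexplained mismatch.
- *That the groups will differ in exposure because the pilot RTs differ.* The daily objective is not described, and both pilot means lie well below 725 ms. A group difference in runs is possible but not shown.
- *That inhibition error will be miscalculated.* The outcome list defines it clearly; the formula has a missing bracket.

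Practice across days is partly covered, since RT is computed by day and repeated-measures modelling is planned.

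**Conclusion.** The point holds in two parts. First, the behavioural accuracy outcome named as primary is not produced by the analysis as described. Only food-cue responses can supply it, and the article neither computes them by category nor settles whether Late and Down count as Hits. That choice could matter: with pilot mean RTs of 450 and 550 ms against a 1.5 s limit, Misses may be few, though the article gives no miss rate. Second, total errors and number of late mix performance with exposure. The distortion equals the ratio of runs played: 1.67 or 2 in the illustrations, which rest on assumed runs, trials and error rates. Its actual size and direction between groups are unknown.

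The session count is a contradiction within the text, and the cue share needs an explanation. Neither changes the sample size. The EEG outcomes and the by-category RT outcome remain defined, apart from the Late/Down question. This should be corrected before analysis; it does not invalidate the study.

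**What to change.** - Define primary accuracy as Hits/(Hits+Misses) on Go trials within each food category, and state whether Late and Down responses are Hits. Bringing the 725 ms threshold into the definition would mix speed into accuracy, so lates are better reported separately.
- Analyse it by fat × carbohydrate × group with a model that handles unequal trial numbers, such as a binomial mixed model with a participant random effect.
- Report errors as a proportion of trials, and lates as a proportion of Hits or of Go trials.
- Keep inhibition error as one outcome without food category, written FA/(FA+CR)×100.
- Optionally add a first-run-only sensitivity analysis of RT and accuracy for practice. As the main analysis it would discard data, and the denominators do not require it.
- Reconcile the session total with one plus nine sessions per visit, and state how often each image is shown so that the Go share can be verified.

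The cost is re-coding from the raw logs and text corrections, with no new data collection, provided the logs identify the food item on Misses as well as on Hits. The definitions should be fixed before group results are examined.
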